## 9.5 Exclusion criteria

Subjects must not enter the study if any of the following exclusion criteria are fulfilled:

1. Pregnant or lactating female.
2. History of any clinically significant disease or disorder including, but not limited to, gastrointestinal, cardiovascular, cerebrovascular, pulmonary, neurologic, renal, liver disease which, in the opinion of the Investigator, may either put the subject at risk because of participation in the study, or influence the results or the subject's ability to participate in the study.

3. Clinically significant hypertension or circulatory disease.
4. History or presence of any bleeding disorder including prolonged or habitual bleeding and subjects who are taking blood-thinning medications such as warfarin within 1 month before the IMP application.
5. Any clinically significant illness, medical/surgical procedure or trauma within 4 weeks of the planned first administration of IMP.
6. Any planned major surgery within the duration of the study.
7. Birthmarks, tattoos or any skin abnormality at the site of wounding, as assessed by the investigator.
8. Skin condition or skin quality that, in the opinion of the Investigator, may increase the risk for abnormal scar formation or other injury to the patient or that may obstruct the conduct of the study assessments.
9. Suspicion of melanoma at the site of the biopsy.
10. Use of topical dermatological drug therapy on arms.
11. History or presence of skin diseases.
12. History of keloid formation of skin scars.
13. Seropositive for human immunodeficiency virus (HIV), Hepatitis B surface antigen (HBsAg), or Hepatitis C virus (HCV) antibodies.
14. Positive screen for drugs of abuse or a positive alcohol result at screening or admission to the research clinic.
15. History of severe allergy/hypersensitivity or ongoing allergy/hypersensitivity, as judged by the Investigator, history or ongoing allergy/hypersensitivity to the adhesive material of the dressings or history of hypersensitivity to drugs with a similar biological substance, a similar chemical structure or class to the IMP or any of the excipients or local anesthetics
16. Regular use of any prescribed or non-prescribed medication including antibiotics (in particular erythromycin, clindamycin or linezolid), antacids, analgesics, herbal remedies, vitamins and minerals within 2 weeks prior to the first application of IMP, except occasional intake of paracetamol (maximum 2 000 mg/day; and not exceeding 3 000 mg/week), at the discretion of the Investigator and nasal decongestants without cortisone or antihistamine for a maximum of 10 days, at the discretion of the Investigator.
17. Use of any vasoactive (constrictor or dilator) medication or any prescription or OTC drugs that could modulate blood flow within 2 weeks of the screening visit. Examples of such drugs include nitroglycerine, antihypertensive drugs, antihistamines, NSAIDs, aspirin and OTC cough/common cold products containing antihistamines and/or either phenylpropanolamine or phentolamine during the study up until Visit 6 in the SAD part and Visit 13 in the MAD part.
18. Use of systemic corticosteroids within 2 months prior to the screening visit.
19. Planned treatment or treatment with another investigational drug within 3 months prior to Day -1 or has participated in any other clinical study that included drug treatment with less than 3 months between administration of last dose and first dose of IMP in this study. Subjects consented and screened but not dosed in previous Phase I studies are not excluded.
20. Current, or history of, alcohol abuse/alcoholism/excessive alcohol use and/or use of anabolic steroids or drugs of abuse as judged by the Investigator.

21. Any use of alcohol within 48 hours of admission to the research clinic.
22. Plasma donation within 1 month of screening or any blood donation or corresponding blood loss during 3 months prior to screening.
23. Investigator considers the subject unlikely to comply with study procedures, restrictions and requirements.
24. Abnormal vital signs at screening after 10 min supine rest defined by either:
  - Diastolic blood pressure <50 or >90 mmHg, or
  - Systolic blood pressure <90 or >150 mmHg, or
  - Pulse <40 or >90 bpm
25. Prolonged QTcF (>450 ms), cardiac arrhythmias or any clinically significant abnormalities in the resting ECG at the time of screening, as judged by the Investigator.
26. Current smokers or users of nicotine products. Irregular use of nicotine (e.g. smoking, snuffing, chewing tobacco) less than 3 times per week is allowed before the screening visit.
27. Investigator or any other team member involved directly or indirectly in the conduct of the clinical study.
28. Malignancy within the past 5 years or resected benign colonic polyps.
29. Regular excessive caffeine consumption defined by a daily intake of >5 cups of caffeine containing beverages.

## 9.6 Restrictions during the study

The subjects must be willing to comply with the following restrictions during the entire study duration *i.e.*, from screening to the Visit 6 of the SAD part and Visit 13 of the MAD part unless otherwise stated below.

### 9.6.1 General restrictions

- Contraception Requirements: The male volunteers are expected to use condom to prevent pregnancy and drug exposure of a female partner and refrain from donating sperm from the date of the first dose until 3 months after the last dose of IMP and until confirmation of negative 6 weeks skin swab and feces analyses concerning *L. reuteri* R2LC and/or pILP100 findings. In addition, they need to ensure that their fertile female partners should use contraceptive methods with a failure rate of < 1% to prevent pregnancy (for details, refer to inclusion criterion No 6). The female volunteers are expected to use a contraceptive method with a failure rate of < 1% to prevent pregnancy (for details, refer to inclusion criterion No 6). Abstinence alone is not defined as a highly effective prevention for men or WOCBP.
- Alcohol: Consumption of alcohol is not allowed within 48 hours prior to all visits to the clinic including the end-of-study visit and during visits at the research clinic.  
In addition, in the MAD, consumption of alcohol is disallowed from the first dose until the subjects leave the research clinic after the last dose.
- Nicotine: Smoking or use of nicotine-containing products is not allowed during the study (from screening to Visit 6 in the SAD part and Visit 13 in the MAD part).

- Xanthine or taurine containing products/beverages: Energy drinks (e.g. Redbull) are not allowed during the study (from screening to Visit 6 in the SAD part and Visit 13 in the MAD part).
- Coffee: Not more than 5 cups of coffee per day will be allowed during the study (from screening to Visit 6 in the SAD part and Visit 13 in the MAD part).
- Blood donation, blood components and organs: The subjects must not donate blood, plasma, other blood components or any organs during the study until 3 months after the last dose of IMP and until confirmation of negative 6 weeks skin swab and feces analyses concerning *L. reutrei* R2LC and/or pILP100 findings.
- Participation in other clinical studies: Study subjects are not allowed to participate in any other clinical study during the study period until 3 months after the last dose of IMP and until confirmation of negative 6 weeks skin swab and feces analyses concerning *L. reuteri* R2LC and/or pILP100 findings.
- Activity: study subjects will abstain from strenuous exercise for 72 hours before each blood collection for clinical laboratory tests.
- Study specific restrictions: Study subjects must refrain from any arm exercise during 14 days after the last IMP application. Shower the day after wound incision and IMP application is allowed but bathing is not allowed until 14 days after the last IMP application. Subjects are not allowed to remove the dressings or the elastic tubular bandage between visits to the research clinic. The tubular bandage should be kept for as long as the wounds need dressing (i.e. at least until Visit 6 [SAD] and Visit 13 [MAD]).

### 9.6.2 *Prior and concomitant therapy*

#### Prohibited medication

Use of any prescribed or non-prescribed medication including antacids, analgesics, herbal remedies, vitamin supplements and minerals and other OTC drugs from 2 weeks prior to the (first) administration of IMP until Visit 6 in the SAD part and Visit 13 in the MAD part is disallowed.

Antibiotic treatment with erythromycin, clindamycin or linezolid is disallowed from 14 days prior to start of IMP administration and should be avoided until at least the 6 weeks follow-up visit in each part (Visit 7 and Visit 14, respectively) provided that the skin swab and feces samples were negative).

Importantly, use of NSAIDS (for example, but not limited to, common pain killers containing acetyl salicylic acid [e.g. Treo, Aspirin and Bamy], diclofenac [e.g. Voltaren and Diclofenac] and ibuprofen [e.g. Ipren and Ibumetin and Ibuprofen]) are disallowed from 2 weeks prior to screening and during the whole study up until and including Visit 6 in the SAD part and Visit 13 in the MAD part.

#### Allowed medication

- Paracetamol in doses up to 3000 mg/day for a maximum of 4 days per week.
- Nasal decongestants without cortisone, antihistamine or anticholinergics for a maximum of 10 days.

Other medications considered necessary for the subject's safety and wellbeing may be given at the discretion of the Investigator during the residential period. Following consultation with the Sponsor, the Investigator will determine whether or not the subject should continue in the study.

## 9.7 Screen failures

Screen failures are defined as subjects who consent to participate in the clinical study but are not subsequently randomized in the study. A minimal set of screen failure information is required to ensure transparent reporting of screen failure subjects. Minimal information includes documentation of signed and dated informed consent form (ICF) and reason(s) for screening failure.

Re-screening can be performed once if any of the following were reasons for screening failure or non-randomization (as judged by the Investigator):

- Practical reasons.
- No significant medical conditions (e.g. influenza, nasopharyngitis).
- Reserve subject in previous cohort.
- Plasma or blood donation outside allowed time windows.

For subjects who are re-screened, a new screening number will be assigned and a new, signed ICF will be collected.

## 9.8 Criteria for subject withdrawal

### 9.8.1 *General withdrawal criteria*

Subjects are free to discontinue their participation in the study at any time and for whatever reason without affecting their right to an appropriate follow-up investigation or their future care. If possible, the reason for discontinuation of consent should be documented.

Subjects may be withdrawn from the study at any time at the discretion of the Investigator for any of the following reasons:

- Severe non-compliance to study protocol procedures, as judged by the Investigator and/or Sponsor.
- Subject is lost to follow-up.
- Significant AEs posing a risk for the subject, as judged by the Investigator and/or Sponsor.
- Withdrawal of informed consent to the use of biological samples.
- Subject takes systemic steroids or NSAIDs within the disallowed time frame as judged by the Investigator.

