| CXCL12 ADA sample                                           |                 | X             |                                                               |                     |                                                         | X                 |                                     | X                                             |                      |                      | X                     | X                        | X                    |
| Wound incision by punch biopsy                              |                 | X                         |                                                               |                     |                                                         |                   |                                     |                                               |                      |                      |                       |                          |                      |
| IMP administration                                          |                 | X                         | X                                                             | X                   | X                                                       |                   |                                     |                                               |                      |                      |                       |                          |                      |
| IMP for viable count                                        |                 | X            |                                                               |                     | X                                          |                   |                                     |                                               |                      |                      |                       |                          |                      |
| Wound/scar photography                                      |                 | X            | X                                                             | X                   | X                                                       | X                 | X                                   | X                                             | X                    | X                    | X                     |                          |                      |

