| Assessment / Day                               | Day -28 to -1   | Day 1                     | Day 2                                                         | Day 3           | Day 5, 8, 10, 12, 15, 17, 19
±1 day on Days 12 to 19 | Day 21
± 1 day | Day 32
± 1 day                   | 6 weeks
± 3 days                           | 3 months
± 1 week | 6 months
± 1 week | 12 months
± 1 week | Once yearly
± 2 weeks | 5 years
± 1 month |
| Feces sample for analysis of L. reuteri |                 | X             |                                                               |                 |                                                         | X    |                                     | X                                             |                      |                      | X                     | X                        | X                    |
| Microcirculation                               |                 |                           | X                                                |                 | X                                          |                   |                                     |                                               |                      |                      |                       |                          |                      |
| Dressing                                       |                 | X                         | X                                                             | X               | X                                                       | X    |                                     |                                               |                      |                      |                       |                          |                      |
| Microbe analysis (dressing collection)         |                 |                           | X                                                | X  |                                                         |                   |                                     |                                               |                      |                      |                       |                          |                      |

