## 8.2 Rationale for study design

The European Medicines Agency (EMA) guideline on strategies to identify and mitigate risks for FIH and early clinical trials with IMPs (EMA/CHMP/SWP/28367/07 Rev. 1) has been considered as have the European Directive 2001/18/EC on the deliberate release into the environment of GMOs and the guidance on the environmental risk assessment of genetically modified organisms from the EMA CHMP/GTWP/125491/06. A 5-year long-term follow-up has been included in line with the recommendations given in EMA/CHMP/GTWP/60436/2007.

The SAD/MAD design of the study is based on the aim to study safety, tolerability and exposure of selected doses of activated ILP100-DP in a limited number of healthy volunteers.

The design is adaptive to allow for flexible dose escalation and involves careful monitoring of the subject's well-being. The study will provide important safety and tolerability data and preliminary efficacy data to support the design of further studies, both in healthy volunteers and in patients.

A placebo control will be used to establish the frequency and magnitude of changes in endpoints that may occur in the absence of active treatment. Subjects will serve as his/her own control receiving both placebo and active treatment on the same occasion. The placebo component consist of the ILP100-DP dilution buffer and the activation peptide SppIP. The dilution buffer contains sucrose, which may have a wound healing effect. Recombinant CXCL12 is not used as placebo since the half-life is too short (approximately 6 seconds) to provide clinically relevant data (Laguri *et al.*, 2007; Lambeir *et al.*, 2001). *Lactobacillus* wild-type is not used as placebo since extensive testing in non-clinical studies have shown that it has no effect on wound healing.

Saline (0.9 % NaCl) will be used as a “no treatment” control for several purposes, 1) all wounds must be treated with a solution to keep the blind, 2) all wounds must be exposed to comparable moisture during the study since moisture is a parameter that affects wound healing and 3) NaCl will identify any wound healing properties of sucrose in the dilution buffer used for both ILP100-DP and placebo.

Randomization will be used to minimize bias in the assignment of treatments to wounds.

Blinded treatment will be used to reduce potential bias during data collection and evaluation of endpoints.

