7. Subjects must agree to refrain from donating blood/blood components and organs from the first dose of IMP until 3 months after the last dose of IMP and until confirmation of negative 6 weeks skin swab and feces analyses concerning *L. reuteri* R2LC and/or pILP100 findings.

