### 9.8.2 *Procedures for discontinuation of a subject from the study*

A subject who prematurely discontinues participation in the study will always be asked about the reason(s) for discontinuation and the presence of any AEs. If a subject withdraws consent,

the investigator must ask the subject if he/she is willing, as soon as possible, to be assessed according to the procedures scheduled for Visit 6 and Visit 13 visit in each part. Any ongoing AEs will be followed as described in Section 11.7.1.14.

The primary reason for discontinuation/early withdrawal must be specified in the end-of-treatment form of the eCRF and final drug accountability must be performed.

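### Section 9.8 does not say whether dosed subjects who stop treatment stay in follow-up, and the MAD early-withdrawal visit omits the ADA, feces and blood samples

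*Protocol*

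**What the plan says.** Section 9.8.1 is framed as leaving the study: "Subjects may be withdrawn from the study at any time at the discretion of the Investigator for any of the following reasons". One listed reason is "Subject takes systemic steroids or NSAIDs within the disallowed time frame as judged by the Investigator". Section 9.6.2 sets the NSAID window as "during the whole study up until and including Visit 6 in the SAD part and Visit 13 in the MAD part", so it covers subjects who have already been dosed.

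Section 9.8.2 provides for a subject who withdraws consent to be asked "to be assessed according to the procedures scheduled for Visit 6 and Visit 13 visit in each part". Footnote 1 to both schedule tables, and the visit descriptions in Sections 8.1.1 and 8.1.2, apply the same visit to any early withdrawal.

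Section 8.4.1 allows the iSRC to recommend that dosing stop in individual subjects, and Table 8.4-1 orders this for certain events. Neither says what then happens to those subjects' follow-up.

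In Table 8.1-2 the row "CXCL12 ADA sample" and the row "Feces sample for analysis of" *L. reuteri* are both blank at Visit 13, as is the row for CXCL12 and *L. reuteri* blood sampling.

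On purpose, Section 8.2 states: "A 5-year long-term follow-up has been included in line with the recommendations given in EMA/CHMP/GTWP/60436/2007". Sections 9.4 and 9.6.1 keep the contraception and donation restrictions in force for 3 months after the last dose and "until confirmation of negative 6 weeks skin swab and feces analyses concerning" the organism or its plasmid.

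**The concern.** The product is a genetically modified organism classed as a gene therapy. ADA formation is a primary endpoint, and Section 6.3 names feces sampling as a way of tracing possible colonies. The value of both depends on observing everyone who was dosed, including those who stop early.

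Two things stand in the way. Section 9.8 does not separate stopping treatment from leaving observation. In the SAD part the only dose is on Day 1, so a later withdrawal changes no exposure and only ends observation. Also, the visit meant to capture a departing MAD subject lacks the samples for these two outcomes. A sample that was never taken cannot be recovered in the analysis, so the SAP cannot repair this.

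**Working it through.** The plan gives no figure on this point, so there is nothing to reproduce. The check sets passages and schedule columns side by side.

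**1. Stopping dosing against leaving the study.** Section 9.8.1 speaks only of withdrawal from the study. Section 8.4.1 and Table 8.4-1 speak of stopping dosing in individual subjects, separately from terminating the study. Section 11.7.1.15 (partner pregnancy) requires both: treatment stops and the subject leaves. Only this last text states what happens to participation when dosing stops. For a subject whose dosing is stopped under Table 8.4-1, the protocol does not say whether later visits continue.

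**2. Who receives the exit assessment.** Section 9.8.2 ties it to withdrawal of consent. The schedule footnote ties it to early withdrawal of any kind. A subject withdrawn by the Investigator is covered by the second text but not by the first.

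**3. What the exit visit contains.** From Tables 8.1-1 and 8.1-2:

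| Sample | SAD Visit 6 (exit) | MAD Visit 12 (Day 21) | MAD Visit 13 (Day 32, exit) | MAD Visit 14 (6 weeks after last dose) |
|---|---|---|---|---|
| ADA | yes | yes | no | yes |
| Feces | yes | yes (Day 15 to 21) | no | yes |
| CXCL12/*L. reuteri* blood | yes | yes | no | no |
| Skin swab | yes | yes | yes | yes |

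The ADA and feces samples listed at MAD Visit 2 precede the first dose (footnote 9). The first post-dose ADA sample is therefore at Visit 12, and the first post-dose feces sample falls between Day 15 and Day 21 (footnote 26). Visit 13 hands out a feces kit, but the next feces sample is at Visit 14.

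**4. Exposure already received.** MAD dosing days are 1, 2, 3, 5, 8, 10, 12, 15, 17 and 19.
- Doses before Day 21: 10 of 10. Withdrawal before Visit 12 can follow the full course and still leave no post-dose ADA result.
- Doses before Day 15: Days 1, 2, 3, 5, 8, 10 and 12, that is 7 of 10, each to 4 active wounds. Withdrawal in this period leaves neither a post-dose ADA nor a post-dose feces result.

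**5. Release from restrictions.** The 6-week samples are taken at Visit 7 (SAD) and Visit 14 (MAD). A subject withdrawn earlier does not attend these visits, so the stated condition for lifting the contraception and donation restrictions cannot be met. This applies in both parts.

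**6. Illustration of size.** With 0 positives in n subjects, the one-sided 95% upper bound on ADA incidence is 1 − 0.05^(1/n).
- n = 8: 31%
- n = 7: 35%
- n = 6: 39%

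The second and third lines assume that one or two subjects in a MAD cohort of 8 have no post-dose sample and are not replaced.

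**The case against.** Several stronger readings are tempting, and the documents do not support them.

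- *The rules remove subjects for a single NSAID intake.* Section 9.8.1 says subjects may be withdrawn, and the NSAID item is left to the Investigator's judgement. A single intake could qualify only because no threshold is set; nothing requires withdrawal.
- *There is no way to stop dosing without leaving the study.* Section 8.4.1 and Table 8.4-1 do allow dosing to stop in individual subjects and do not say that those subjects leave. The defect is that Section 9.8 does not take this up, so their follow-up status is undefined.
- *Each withdrawal costs 1/8 (12.5%) of a MAD cohort or 1/4 (25%) of a SAD cohort.* Section 9.8.2.1 permits replacement up to Visit 6 or Visit 13, except after AEs at least possibly related to the IMP, so these fractions do not simply follow. Replacement may restore the cohort's size, but it does not supply the dosed subject's own results.
- *Long-term results will describe those who tolerated treatment best.* Nothing in the protocol shows why subjects would take NSAIDs or how many would be withdrawn, and paracetamol is allowed. This remains speculation.

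It is also fair that much monitoring remains. Visit 13 includes a skin swab, physical examination and safety laboratory tests. A MAD subject leaving on Day 12 already has CXCL12 plasma samples from Days 1, 2, 3, 5 and 8 and blood cultures from Days 3, 5 and 8. Ongoing AEs are followed, and SAEs are followed until recovery or stabilization. Section 9.8.1 preserves a right to appropriate follow-up, although it names no visits.

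These points narrow the concern to the undefined follow-up status and to specific missing samples. They do not remove it: SAD Visit 6 shows that the sponsor wanted these samples at exit, and no reason is given for omitting them after repeated dosing.

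**Conclusion.** The point holds in a limited form and is worth correcting. Sections 8.4.1, 9.8.1 and 9.8.2, Table 8.4-1 and footnote 1 of the schedules leave two things unsettled: whether a subject whose dosing stops remains in follow-up, and who is offered the exit visit. They must be reconciled.

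Separately, the MAD exit visit omits ADA, feces and CXCL12/*L. reuteri* blood. The ADA gap applies to withdrawal before Visit 12 and the feces gap to withdrawal before the Day 15 to 21 sample; a later withdrawal leaves one post-dose result of each. The SAD part does not share this sampling gap. The missing 6-week samples affect both parts.

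The size per subject is definite: no post-dose result on one primary endpoint and, before Day 15, none on gut shedding. The size for the study is unknown, because the documents give no expected withdrawal rate. The conclusion assumes that a withdrawn subject attends the exit visit as scheduled and no later visit.

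**What to change.** Leave every clinical criterion for withdrawal and for stopping dosing as it stands.

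1. In Section 9.8, state that stopping IMP is distinct from leaving the study. Add that subjects who received at least one dose and have not withdrawn consent are asked to continue the scheduled safety and long-term follow-up visits. Cross-refer to Section 8.4.1 and Table 8.4-1, and reconcile the new text with Section 11.7.1.15.
2. Align Section 9.8.2 with footnote 1 of Tables 8.1-1 and 8.1-2, so that the exit assessment is offered after any early withdrawal.
3. Add a footnote to Table 8.1-2: when Visit 13 serves as an early-withdrawal visit before the Visit 12 samples were taken, the ADA and feces samples and the Visit 12 blood sample are collected.
4. Reconcile the restriction wording in Sections 9.4 and 9.6.1 with the case of a subject who leaves before the 6-week visit. No rule is proposed here.

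The cost is protocol wording and up to three extra samples per early-withdrawn MAD subject. These sample types are already in the study, and the follow-up visits were already planned for these subjects.
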